### Acute cohort

A prospective cohort of patients newly diagnosed with cancer who received anthracycline chemotherapy has been recruited from clinics at the four pediatric participating centres (recruitment target *n* = 270; recruitment actual *n* = 307). We will assess whether genetic predictors of anthracycline susceptibility, biomarkers of early cardiac damage, and imaging parameters of acute cardiac dysfunction predict which patients will demonstrate evidence of persistent or progressive cardiac damage at the 12 months follow-up from their last cycle of anthracycline chemotherapy (See Fig. 1 for timeline of sample and data acquisition in Acute Cohort). Eligibility criteria for both cohorts are provided in Table 1.

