### Developing a risk prediction model

To achieve the primary objective of the Acute Cohort study (identifying patients at increased risk for therapy-induced cardiac disease prior to starting or during therapy), evolution of echocardiographic parameters over the treatment duration will be modeled in linear and non-linear regression models adjusted for repeated measures through a compound symmetry covariance structure. The resulting general estimating equations (GEE) will provide an estimate of the effect of anthracyclines over time for the entire cohort and the parameter estimate (slope of change over time) for each individual patient will be used as a potential predictor of therapy-induced cardiac damage. Twelve months after their final cycle of anthracycline chemotherapy, patients will be classified as having cardiac disease or not based on evidence of remodeling or decreased EF or CHF. Potential factors associated with acute cardiac change or cardiac damage at 12 months after treatment will be sought from patient demographics (e.g. age at treatment, gender), treatment (e.g. cumulative anthracycline dose, radiation exposure), genomics, serial biomarkers and echocardiographic measurements at baseline and during follow-up. Because of the very large number of potentially associated factors (and the multiple variations in format/time points for many factors), we will have to reduce the number of candidate factors using a pre-specified algorithm. As exploratory analyses, univariate regression models using therapy-induced cardiac changes or cardiac disease at 1 year (present vs. absent) as the dependent variable, and all other collected variables as potential independent variables will be created. This will allow exploration of variables potentially associated with therapy-induced cardiac damage including assessment of collinearity, ill condition (variables with no events in one of the study groups) or amount of missing data. All variables with univariable *p*-value <0.30, excluding collinear variables, ill conditioned variables or variables with an unacceptable amount of missing data will be included in a bootstrap bagging algorithm. A total of 5000 random sub-samples will be created and for each of those, a mixed stepwise regression model will be used to obtain multivariable predictors for therapy-induced cardiac damage. The proportion of sub-samples in which a given variable is selected is called reliability. Variables with high reliability (>50%) will then be included in a multivariable regression model with backward selection of variables to obtain a final model. This algorithm significantly improves the accuracy of variable selection, reduces the probability of sampling bias and corrects for multiple comparisons better than a post-hoc analysis would. At the end of this algorithm we will be left with a limited number of associated factors, all with high reliability. Based on the reliability estimates, we will be able to determine whether the risk of therapy-induced cardiac changes or cardiac damage at 1 year after anthracycline exposure is driven by baseline measurements (including clinical, genomic, echocardiographic or biomarkers), by reaching specific milestones during anthracycline treatment, by change over time in cardiac dimension/function and biomarkers during anthracycline treatment, or by a combination of all three.

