
## Discussion

Cardiac disease is the third leading cause of premature death in CCS, with a 7-fold increased risk of premature cardiac death as compared to the general population [14]. By the time clinical or imaging evidence of cardiac dysfunction becomes apparent, it is often late in the natural course of the disease making it difficult to intervene and reverse existing damage. The need to develop more sensitive techniques that will allow for earlier detection of anthracycline-induced cardiac toxicity is critical.

Findings from this research study may be able to inform clinical decision making through a risk prediction algorithm that will assist in identifying patients who are at an increased risk of anthracycline-induced cardiac toxicity. It is likely that combining genetic predictors of susceptibility with clinical risk factors will allow for a more personalized approach to identifying at-risk patients prior to initiating anthracycline therapy. This will allow for the modification of cancer therapy to prevent or reduce the risk of cardiac disease, allowing for optimal long-term outcomes in this patient population.

This cohort will provide an unparalleled resource for future research by providing not only a data resource, but also a risk prediction model, that will enable other investigators with an interest in cardiac late effects resulting from childhood cancer treatments to perform further investigation in the field.

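### The selection algorithm for the risk model is credited with correcting for multiple comparisons, but no step in it adjusts for the number of candidates

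*Protocol article*

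**What the plan says.** The section Developing a risk prediction model in the Protocol article fixes the steps in order.

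- **Candidate pool.** The reduction is needed "Because of the very large number of potentially associated factors (and the multiple variations in format/time points for many factors"). Univariable models with "all other collected variables as potential independent variables will be created".
- **Screen.** "All variables with univariable *p*-value <0.30, excluding collinear variables", ill-conditioned variables and those with too much missing data, go forward.
- **Resampling.** "A total of 5000 random sub-samples will be created", with mixed stepwise regression in each. The share of sub-samples that select a variable is called its reliability.
- **Final model.** "Variables with high reliability (>50%) will then be included in a multivariable regression model with backward selection of variables".

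The section then claims that the algorithm improves the accuracy of variable selection and "reduces the probability of sampling bias and corrects for multiple comparisons better than a post-hoc analysis would". It describes every surviving factor as highly reliable. It also plans to use the reliability estimates to decide whether risk is driven by baseline measurements, by milestones during treatment, by change over time, or by all three.

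**The concern.** A procedure corrects for multiple comparisons if its criterion for keeping a variable becomes stricter as more variables are tried. None of the thresholds here (0.30, the stepwise entry level, 50%, the backward level) is tied to the number of candidates.

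As described, the screen precedes the resampling and is run on the full data. The resamples are drawn from the same patients, and the backward fit uses those patients again. A chance association in the cohort is therefore carried into every resample. Reliability shows how stable an association is within this sample, not whether it would appear in another.

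The integrated model is one of the study's four aims, and the Discussion presents it as "a risk prediction model, that will enable other investigators" to do further research. If reliability above 50% is read as protection against false selection, noise variables may be reported as reliable predictors, and the conclusion about what drives risk would inherit them.

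**Working it through.** The article gives no error rate for the algorithm, so there is no figure to reproduce. The check asks how often the algorithm keeps a predictor when none is real.

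**Inputs from the article.** Acute Cohort size ("recruitment target *n* = 270; recruitment actual *n* = 307"; 307 used), screen at p<0.30, reliability above 50%, backward refit, binary outcome at 12 months.

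**Assumed, because not stated.** Number of candidates k = 10 to 200; event rate 20% (10% and 30% also run); stepwise and backward thresholds 0.05 (0.01 and looser also run); bootstrap resamples of size n (63.2% sub-samples without replacement also run); independent candidates (correlation 0.3 also run).

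**Step 1: what the 50% rule amounts to.** In a bootstrap resample, a variable's test statistic is roughly normal around its full-sample value z, with variance 1. It is reselected in more than half of resamples when |z| exceeds the entry value. At entry level 0.05 this means |z| > 1.96, a full-sample p below 0.05. A variable at the screen limit (p = 0.30, |z| = 1.036) is reselected in about 18% of resamples, so by this approximation the screen removes little that the 50% rule would have kept.

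**Step 2: benchmark.** For k independent tests at 0.05, P(at least one false positive) = 1 − 0.95^k. This gives 0.40, 0.64, 0.92 and 0.994 for k = 10, 20, 50 and 100.

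**Step 3: simulation of the algorithm on pure noise.** Per scenario, 200 to 1000 data sets were run with 100 to 200 resamples each instead of 5000, using a linear approximation to the logistic model. Base case:

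| k | P(at least one noise predictor kept) | Mean number kept | Plain stepwise at 0.05 | Bonferroni |
|---|---|---|---|---|
| 10 | 0.37 | 0.5 | 0.40 | 0.06 |
| 20 | 0.61 | 0.9 | 0.66 | 0.05 |
| 50 | 0.89 | 2.2 | 0.93 | 0.04 |
| 100 | 0.98 | 4.1 | 0.996 | 0.05 |
| 200 | 1.00 | 7.1 | 1.00 | 0.05 |

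Logistic stepwise gave 0.59 at k = 20 and 0.86 at k = 50. Event rates of 10% and 30% at k = 50 gave 0.88 and 0.89. A second, separate simulation of the base case gave 0.57, 0.90 and 0.98 at k = 20, 50 and 100, against 0.62, 0.93 and 0.99 for plain stepwise.

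**Step 4: other assumptions.**

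| Change from base case | k = 20 | k = 50 | k = 100 | k = 200 |
|---|---|---|---|---|
| Correlation 0.3 | – | 0.52 | 0.68 | 0.86 |
| 63.2% sub-samples | – | 0.41 | 0.71 | 0.90 |
| Thresholds 0.01 | 0.15 | 0.25 | – | 0.74 |
| Stepwise 0.15, final 0.10 | – | 1.00 | – | – |

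(– means not run.) The second simulation gave 0.45 with 63.2% sub-samples at k = 50.

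Sub-sampling lowers the rate because z shrinks by √0.632 = 0.795 in each sub-sample. The 50% rule then needs |z| > 1.96/0.795 = 2.47, p about 0.014. With that level, 1 − (1 − 0.0137)^k is 0.50, 0.75 and 0.94 for k = 50, 100 and 200, somewhat above the simulated values. The criterion is stricter, but it is still fixed and does not respond to k. At 0.01 thresholds the benchmark 1 − 0.99^k is 0.18, 0.39 and 0.87 for k = 20, 50 and 200, against the simulated 0.15, 0.25 and 0.74.

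**Step 5: apparent performance.** When noise was kept in the base case, the AUC in the same patients averaged 0.61, 0.65, 0.69 and 0.75 for k = 20, 50, 100 and 200, against 0.50 in new data.

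**The case against.** **The claim is comparative.** The article says only that the algorithm does better than an unspecified post-hoc analysis. Against plain stepwise it does keep noise less often. With bootstrap resamples and independent candidates the gain is a few points. With true sub-samples it is large (0.41 against 0.93 at k = 50), and with correlation 0.3 it is also material (0.52 against 0.81 at k = 50). The text uses both bootstrap and sub-sample language, so either scheme may be meant. This stands as a limit on the size of the effect. It does not rescue the claim: a lower rate that still climbs with k is not a correction for multiplicity, and Bonferroni held 0.04 to 0.06 throughout.

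**The frequency rests on missing inputs.** A reader might infer that the algorithm keeps noise almost every time. The article does not support that: the number of candidates, entry level, sub-sample size and event rate are not given, and reasonable choices bring the rate well down. The high end fits a very large pool of weakly correlated candidates; serial measurements may well be correlated even after collinear variables are removed.

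**Optimism correction.** A reader might also infer that the plan omits it and will publish an inflated AUC. This is a condensed article, internal validation is commonly left to the analysis plan, and no AUC is promised. The silence is supporting context, not a separate error.

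**Safeguards elsewhere.** The Genomics Core has a replication cohort and the Biomarker Core a validation cohort from other sites. These cover gene and marker findings, not the integrated model. That markers already selected by the cores re-enter as candidates is an inference, not stated text.

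**Global null.** Some predictors are established, so an all-noise setting is a benchmark, not a forecast. Real predictors would not, however, remove the false selections among the noise candidates.

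**Conclusion.** The point holds in limited form. The article attributes to its algorithm a property that the described steps do not have. This is stated text, not missing detail. With bootstrap resamples, reliability above 50% is roughly an unadjusted test at the stepwise entry level. Under the base assumptions, the chance of keeping at least one noise predictor is 0.37 to 0.61 with 10 to 20 candidates and 0.89 to 1.00 with 50 to 200. With correlated candidates, 63.2% sub-samples or 0.01 thresholds it is about 0.15 to 0.90. It stayed above 5% in every scenario run. These figures show the size of the problem under stated assumptions and do not predict this study's own error rate. The part of the claim about sampling bias was not tested by any calculation, though nothing described supports it either, since all resamples come from the same patients.

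**What to change.** 1. Delete the multiplicity claim, or replace it with a statement that reliability measures how stably a variable is selected within this sample and does not control false selection. Soften in the same way the description of surviving factors and the plan to infer from reliability what drives risk.
2. Set the reliability cut-off by running the full pipeline, screen included, on data sets with the outcome permuted, and choose the value that holds false selection at a stated level.
3. Base any reported model performance on the full pipeline (screen, stepwise, cut-off, backward fit) repeated inside an outer bootstrap or cross-validation loop.

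Elastic net instead of stepwise selection, and forcing in the established clinical predictors, are reasonable preferences but not needed to correct the error.

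The cost is computing time and wording, with no new patients or data. The downside is fewer retained predictors and lower reported performance.

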
## Discussion

Cardiac disease is the third leading cause of premature death in CCS, with a 7-fold increased risk of premature cardiac death as compared to the general population [14]. By the time clinical or imaging evidence of cardiac dysfunction becomes apparent, it is often late in the natural course of the disease making it difficult to intervene and reverse existing damage. The need to develop more sensitive techniques that will allow for earlier detection of anthracycline-induced cardiac toxicity is critical.

Findings from this research study may be able to inform clinical decision making through a risk prediction algorithm that will assist in identifying patients who are at an increased risk of anthracycline-induced cardiac toxicity. It is likely that combining genetic predictors of susceptibility with clinical risk factors will allow for a more personalized approach to identifying at-risk patients prior to initiating anthracycline therapy. This will allow for the modification of cancer therapy to prevent or reduce the risk of cardiac disease, allowing for optimal long-term outcomes in this patient population.

This cohort will provide an unparalleled resource for future research by providing not only a data resource, but also a risk prediction model, that will enable other investigators with an interest in cardiac late effects resulting from childhood cancer treatments to perform further investigation in the field.

## Abbreviations

CCS: Childhood cancer survivor
CHF: Congestive heart failure
CMR: Cardiac Magnetic Resonance
ECV: Myocardial extracellular volume
EF: Ejection fraction
GEE: General estimating equations
LV: Left ventricular
LVEF: Left ventricular ejection fraction
LVPWT: Left ventricular posterior wall thickness
REDCap: Research Electronic Data Capture
SF: Shortening fraction
SNPs: Single nucleotide polymorphisms
TDR: Thickness to dimension ratio
